### Economic evaluation

We will develop a costing toolkit to provide transparent resource use and costs for the delivery of the standard care and digital delivery pathways. The toolkit development process will comprise three stages: planning, data collection, synthesis and analysis.^33 34^ We will require resource use and cost estimates for delivery of W8Buddy providing weight management medication and standard of care (Tier 3 WMS). We will produce a systematic review of cost-effectiveness literature to inform the development of a decision-analytic model. The model will be used to estimate the cost-effectiveness of Tier 3 WMS in addition to W8Buddy compared with WMSs delivering weight management medication to support people with obesity. This will be fundamental to help to understand the long-term cost-effectiveness of weight management programmes as they allow for the extrapolation of the short-term benefits of interventions.

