#### Research question

What is the long-term (18-month) impact on clinical outcomes, including health-related quality of life (QoL) and cost-effectiveness of W8Buddy with and without weight management medication and lifestyle support to people living with obesity, compared with WMS standard care?

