### Study setting and sites

This study will run at four NHS sites (UHCW, UHB, LLT, HDUHBT). Standard care differs across the recruiting sites, including the mixed provision of obesity medication. Sites without medication as standard care will be noted as the digital pathway without medication.

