**Figure 1 F1:**
[figure not shown]
Participant flow chart. The flow chart describes where participants will be providing data in both the digital and standard of care arms. PI, principal investigator.

Eligible participants will be able to choose how they receive their WMS—either in the standard NHS delivery, or via fully digital platform Gro Health W8Buddy. Site-specific standard of care pathways will be delivered by the usual healthcare professionals, employed by each NHS site. The digital pathway will be delivered by healthcare professionals employed by DDM (providers of Gro Health W8Buddy). We aim to recruit a total of 450 participants across both arms from September 2025 to February 2026.

Those who satisfy the study inclusion criteria will be contacted by the research team via telephone. Brief information about the study will be provided to potential participants, including a link to a website with information about the study. This website will be password protected as only eligible participants will be able to view it. Digital information sheets and consent forms will be hosted on the website.

If a patient is unable to access the website (therefore, unable to complete electronic consent), the local site research nurse will invite them to the hospital. They will show the participant the research website and help them with electronic consent. Later, the research nurse will print out the consent form (signed copy) only for the patient if they do not have access to email.

Electronic consent for data collection, with an option to consent for ongoing data collection, will be obtained. Following informed consent, participants will be able to choose the digital or standard care pathway via the website. A copy of the signed consent form will be sent to the participants, local research team and site principal investigator (PI).

To support data collection in the standard care pathway, participants will be offered a £10 voucher for each completed survey at months 0, 6, 12, 18 and 24; vouchers will not be provided for sign up only, surveys must be completed by participants.

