### Standard care

Participants in the standard care arm will receive the tier 3 WMS that is delivered by their local NHS trust. All four NHS trusts included in the research have differences in their tier 3 service, which will be explored in detail as part of the study. The differences range from the amount of input from healthcare professionals (psychologist, dietitian, physician), modality of sessions (1–1 or group sessions) and frequency. Post study care for participants in standard care will be delivered in accordance with their NHS trust policies for tier 3 wt management. As discussed previously, the W8Buddy intervention is included in the standard of care at the lead centre (UHCW). It is used as a digital support tool only (no access to clinicians via W8Buddy), enhancing the usual face-to-face care, and as such, differs from entirely remote digital pathway. For this reason, the model of delivery of care is hybrid at UHCW (refer to table 1 for further detail).

**Table 1 T1:** Standard of care

NHS site	Standard of care	Weight management medication offered in current tier 3 service*
UHCW	Hybrid standard of care with digital W8Buddy input and in person MDT support. Mixture of one-to-one and group sessions delivered by dietitians, psychologists and consultant endocrinologists.	No
UHB	Mixture of group sessions and one-to-one appointments delivered by dietitians, psychologists and consultant endocrinologists following a face-to-face introductory group session.	No
LLT	Mixture of face-to-face and group sessions delivered by psychologists, dietitians and consultant endocrinologists.	No
HDUHBT	Mixture of face-to-face and group sessions delivered by psychologists and dietitians. After completion, they are seen by a consultant.	Yes

*Please note this information is accurate at time of publication.

HDUHBT, Hywel Dda University Health Board Trust; LLT, London Luton Trust; MDT, multidisciplinary team; UHB, University Hospitals Birmingham; UHCW, University Hospital Coventry & Warwickshire.

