### Outcomes

The primary outcome is changes in body weight after 18 months of using either (1) a fully digital weight management programme (remote digital pathway Gro Health W8Buddy) or (2) site-specific delivered weight management programmes incorporating face-to-face and/or virtual group sessions (standard care).

Secondary outcomes are metabolic markers (HBA1c, lipids), blood pressure, waist circumference and health-related QoL (EQ-5D-5L).^28^

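### The economic model's stated comparison (W8Buddy as an add-on, against services that deliver medication) contradicts the research question, the study arms and the model's own cost inputs

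*Protocol article*

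**What the plan says.** The protocol article describes the economic comparison in several places.

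- **Research question:** the target is "cost-effectiveness of W8Buddy with and without weight management medication and lifestyle support to people living with obesity, compared with WMS standard care".
- **Screening, recruitment and consent:** participants choose their service "either in the standard NHS delivery, or via fully digital platform Gro Health W8Buddy".
- **Outcomes:** the first arm is "a fully digital weight management programme (remote digital pathway Gro Health W8Buddy"), and the second is the programme each site delivers as standard care.
- **Economic evaluation, costing toolkit:** it will give "resource use and costs for the delivery of the standard care and digital delivery pathways".
- **Economic evaluation, cost inputs:** "We will require resource use and cost estimates for delivery of W8Buddy providing weight management medication and standard of care (Tier 3 WMS").
- **Economic evaluation, model:** "The model will be used to estimate the cost-effectiveness of Tier 3 WMS in addition to W8Buddy compared with WMSs delivering weight management medication".

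Two further places bear on how the model sentence is read. Under Standard care, the article says of W8Buddy at UHCW: "It is used as a digital support tool only (no access to clinicians via W8Buddy), enhancing the usual face-to-face care". It adds that this differs from the wholly remote pathway. Table 1 lists medication in the current tier 3 service at HDUHBT and not at UHCW, UHB or LLT. Under Study setting and sites, the article says: "Sites without medication as standard care will be noted as the digital pathway without medication".

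**The concern.** The model sentence is the article's only statement of which strategies the model will compare, and both of its sides differ from the study. Its intervention is tier 3 care plus W8Buddy, whereas the cohort studies W8Buddy in place of local tier 3 care. Its comparator is services that deliver medication, whereas the cohort's comparator is standard care as each site provides it, which mostly excludes medication.

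Cost-effectiveness is part of the research question and of the first objective, and the outputs are meant for NICE and for commissioners. The Discussion argues for the digital pathway partly because patients might no longer need to attend in person, with the costs that brings. Only a model of substitution can test that argument. If medication also sits on one side only, its cost and effect cannot be separated from those of digital delivery.

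**Working it through.** The article gives no figure to reproduce, so the check sets the statements side by side.

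| Section | Intervention | Comparator | Where medication sits |
|---|---|---|---|
| Research question | W8Buddy | WMS standard care | W8Buddy both with and without it |
| Screening; Outcomes | Fully digital pathway | Site-specific standard care | Not specified |
| Study setting; Table 1 | Digital pathway, noted as without medication where standard care has none | Standard care, medication listed at one of four sites | Appears to follow the site |
| Economic evaluation, toolkit | Digital pathway | Standard care | Not specified |
| Economic evaluation, cost inputs | W8Buddy providing medication | Standard tier 3 care | W8Buddy side |
| Economic evaluation, model | Tier 3 care plus W8Buddy | Services delivering medication | Comparator side |

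The last row is the only one in which W8Buddy is an addition to tier 3 care, and the only one in which delivering medication defines the comparator.

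Simple notation shows why this matters. Let T be the cost of local tier 3 care, R the cost of the remote pathway with its own clinicians, P the cost of W8Buddy as a support tool, and M the cost of medication. For illustration, assume that costs add and that T and M are the same wherever they occur.

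1. **Study arms, medication following the site.** With medication on both sides: (R + M) − (T + M) = R − T. With medication on neither side: R − T. The increment is remote delivery against local delivery.
2. **Cost-input sentence, where standard care has no medication.** (R + M) − T = (R − T) + M. Delivery mode and medication are mixed.
3. **Model sentence read literally, add-on without medication.** (T + P) − (T + M) = P − M.
4. **Model sentence read literally, add-on with medication.** (T + P + M) − (T + M) = P.

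In lines 3 and 4, T cancels and R never appears. On that reading the increment contains nothing about replacing local care with remote care, and in line 3 it also subtracts the cost of medication. The same structure applies to effects: an add-on effect is not a substitution effect, and a medication effect on one side only is confounded with delivery mode.

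As illustration only, the literal phrases can be matched to the standard-care services in Table 1. Tier 3 care combined with W8Buddy matches only the UHCW hybrid, and delivery of medication matches only HDUHBT.

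**The case against.** The strongest reply is that this is one loose sentence in a condensed article. The two sentences before it describe the study's own two pathways, so the intent is probably right. The wording could also be read at service level, as a tier 3 service that adds the remote option. The Objectives speak of bringing a digital pathway into existing services, and the Discussion of its uptake within standard care.

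Part of this stands. The contradiction lies within one section and is not a settled plan to leave out the remote pathway. It would also be wrong to say that the toolkit costs only W8Buddy with medication, because its opening sentence covers both pathways. The service-level reading, however, repairs only the intervention. The comparator remains services delivering medication, which is neither the research question's comparator nor that of the cost inputs. Nor does condensation excuse it: the objection is to a comparison that is stated and conflicts with the rest of the article, not to missing detail on model structure or horizon.

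A reader might go further and infer that the model will compare UHCW hybrid care with HDUHBT, and so be wholly confounded by site, use no fully digital participants and rest on an unpowered group. The document does not support this. No section says the model compares those sites. The model is decision-analytic and informed by a literature review, so its strategies need not be single recruiting sites. The comparator is written in the plural, and Table 1 is noted as correct only when published. The unpowered label belongs to the secondary clinical comparison of the hybrid. Group sizes for such a contrast would need site and uptake splits that the article does not give.

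**Conclusion.** The point holds as an internal contradiction. The model sentence conflicts with the Research question, with the arms under Screening, recruitment and consent and under Outcomes, and with the cost inputs in its own section. A model built to that sentence would estimate the value of an add-on against medication-delivering services, mix medication with mode of delivery, and leave the cost-effectiveness of the remote pathway against standard care unanswered.

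The conclusion rests on the text alone. It depends on no sample size, site split or uptake rate, and the algebra only illustrates it under additive costs. The site matching is likewise illustrative. The consequence is confined to the economic objective, but there it determines which question is answered, so it should be settled before the model is built.

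**What to change.** Reconcile the Economic evaluation section with the Research question and the arms, as follows.

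1. State the decision problem as the fully remote W8Buddy pathway against site-specific standard tier 3 care.
2. State the medication status of each strategy, so that medication does not differ between the sides unnoticed, and show results with and without medication as the Research question asks.
3. Keep the UHCW hybrid apart from the standard-care comparator, as the Sample size calculation and the Primary and secondary outcome analysis already do.
4. Align the cost-input sentence with these strategies, so that W8Buddy without medication is named as well as W8Buddy with it.

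If the authors did intend a service-level strategy in which tier 3 services offer the remote option, they should say so explicitly and define it separately from the head-to-head comparison.

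The cost is rewording and a little extra analysis for the results by medication status. No new data are needed, since the toolkit is already meant to cover both pathways and sites will already extract medication use for the control pathway.

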#### Long-term follow-up analysis

Outcomes collected beyond the 18-month primary outcome will be analysed at a later stage, subject to further funding. The aim of the longer-term follow-up is to explore the long-term impact of digital weight management interventions. We expect the analyses will be done similarly to our primary and secondary clinical and health economic analyses.

### Process evaluation

A mixed methods process evaluation will be conducted to understand the implementation of W8Buddy. Process evaluation data are listed in online supplemental table 1.

Electronic data from intervention and control pathways: We will collate data from the electronic clinical records, intervention and study records of all study participants on:

Fidelity: Delivery of coaching sessions, check-ins and physical activity sessions and progress reviews.Adherence: Including biomedical explanations of adherence (comorbidities), we will assess user adherence to each consultation in the digital pathway (a patient attending 75% of consultations or more is considered adherent).Who chooses the digital pathway or not.Who engages with the digital pathway, their level of engagement and predictors of engagement.

### Qualitative data collection and analysis

We will record observation data as field notes and collate documents. Qualitative data will be obtained from participants’ interviews via telephone or videoconference. We will audio record the interviews, transcribe using software and check the transcripts against the audio recording. We will undertake thematic analysis, with independent quality checks.^35^ This analysis will be undertaken independently of the quantitative analysis team.

#### Initial implementation and health professional experience of delivering digital pathway

We will observe site team meetings and implementation of the intervention, access team documents and undertake interviews with team members implementing the digital pathway to understand how they are meeting implementation challenges, training delivered and quality assurance processes put in place. During the observations, the patient will be asked for permission for the researcher to remain present during the health professional-patient interaction. If this is refused, the researcher will leave.

In months 12 and 18, we will interview those delivering the digital pathway to understand their experiences, how they adapt WMS and any unexpected pathways or consequences (estimate 5/site). We will use implementation frameworks^36^ to guide thematic analysis of implementation data while remaining alert to new themes. Early analysis of data on implementation will be used to provide formative feedback for subsequent intervention site teams.

### User experience of digital pathway

In semistructured interviews with users, we will explore their experiences of engaging with the digital pathway, influences on their engagement, challenges and how these were met, adaptations, impact and mechanisms of impact (estimate 10/site, total 40).

We will undertake brief structured interviews with participants not choosing the digital pathway (5/site) and participants not adherent to the digital pathway and/or medicine (5/site). We will ask participants why they did not choose the digital pathway/drop out or return to the digital pathway/medicine. We will develop our brief structured questions with input from the study PPI group to ensure neutral, non-judgemental phrasing. We will sample participants consecutively across study sites and approach them for recruitment at least a week after their decision.

### Describing the control intervention patient pathway

A researcher will visit each site to observe the control intervention. The team providing the control intervention will provide a written description of the control intervention patient pathway. From observation and conversation, the researcher will add additional details and variation on that pathway. The study team will analyse the observation notes to compile a description of the control intervention and check this with staff delivering the control intervention. Study sites will extract from the appointment system and relevant clinical records of their control intervention pathway, patient adherence data in terms of attendance at appointments, whether they are individual or group and duration of appointments, and use of medication.

### Ethics and dissemination

Ethical approval for this study has been obtained from the Health Research Authority (HRA) Research Ethics Committee (REC) and Health and Care Research Wales (HCRW) (REC reference: 25/EM/0147) (online supplemental figure 3). Informed consent will be required to enter the study, as well as to share anonymised data with local healthcare team and study team. Participants will be consented to long-term follow-up using routinely collected data. Protocol amendments (if any) will be reported and discussed with National Institute for Health and Care Research (NIHR) and local ethics committee.

10.1136/bmjopen-2025-109111.supp3Supplementary data

Study data will be collected on the screening logs, W8Buddy App and validated questionnaires (see online supplemental table 1) electronically. Health record data for each site will be accessed by the local research team. An Electronic Data Capture system will be used to record and store study data transferred securely from the W8Buddy App and hospital medical records. This will be the main Study Database. Only research team members and members of the DDM team will have access to it. They will be listed in the delegation log and must hold GCP certification. Audio recordings of interviews will be stored on secure University of Warwick computers and accessed only by the research team located at Warwick.

We have a tiered approach to dissemination to ensure our findings reach participants, policy makers and practitioners. We will host a stakeholder engagement dissemination event at the end of the study to maximise the reach of our findings.

Our results will inform UK guidelines (incorporation of digital tool delivering pharmacotherapy into obesity management guideline). Academic publications will include a protocol paper, main results of RWE evaluation, the health economic assessment and a paper describing the scale-up in NHS services and impact on multiple long-term conditions. We will create an NHS business case, build on ongoing partnership developed across four adoption sites, produce equality and health inequality impact assessment, and have evidence for health and financial impact to support NHS adoption. We will improve NHS services by facilitating the testing and scale-up of our digital innovation which can support other Trusts wanting to deliver digitally enabled services. This will include recommendations to other service providers, targeted education and creation of a virtual learning environment (hosted by an established Warwick University platform). Our study outputs will provide evidence to apply for a NICE review of clinical guidelines and an update to NHS reimbursement criteria, which will open the door to national adoption by WMSs.

## Discussion

Research is needed to determine how we can most effectively deliver WMS to more people.^21^ One potential solution to address issues of patient access is the introduction of digital services.^14–18^ However, long-term evidence about clinical and cost-effectiveness is required before digital pathways are fully integrated into NHS WMS across the whole country.

In this study, we aim to provide longer-term RWE of the clinical and cost-effectiveness, as well as barriers and facilitators of uptake of W8Buddy digital pathway implemented in four NHS sites. All these potential findings are essential considering the current data on the demand for WMS, as well as the health and economic impact of obesity.^2 3^ Guidance on the incorporation of weight management drugs alongside digital interventions is also an unclear gap we intend to fill with our research. With capturing the variation that exists among our four NHS sites, we will provide guidance on implementation into further NHS sites.

Allowing study participants to choose their own pathway will allow RWE to understand uptake of the digital pathway when incorporated into standard care. Furthermore, we are assessing whether W8Buddy can decrease NHS waiting times and costs. Individuals living with obesity could, in time, be supported virtually without the need to attend in person specialist services with the associated costs and challenges of access. Investigating pathways, waiting times and accessibility is important for obesity research considering the low retention rates and high demand but low availability in WMS.^7 11 12^ The use of a digital pathway will also provide further insight for innovative diagnostic pathways for obesity management, such as moving from acute to home care and being offered to more patients in a cost-effective way, which would further contribute to the literature base.

We acknowledge the challenges that may occur with the adoption of a digital pathway into NHS sites such as recruitment rates, levels of engagement and differences in WMS at NHS sites. However, capturing any challenges that may arise and providing solutions will benefit the future implementation of W8Buddy and contribute to generalisable knowledge. Our design means that we will not have matched cohorts across treatment arms, meaning both known confounders (eg, age, BMI) and unknown factors may influence outcomes. To address this, our planned analyses will incorporate statistical adjustments to account for these differences as far as possible. We recognise the limitations of this approach, but it is consistent with the pragmatic design and will allow us to report findings that are representative of real-world practice.

We aim to improve NHS Specialist WMS services by facilitating the evidence generation and scale-up of digital innovation Gro Health W8Buddy. This could, in turn, support other NHS organisations wanting to deliver digitally enabled services. The findings of this study will be used to generate recommendations for other service providers, targeted education and creation of a virtual learning environment. It is aimed that the study outputs will provide evidence needed for full NICE technology appraisal, as well as evidence for NHS commissioners to facilitate national adoption of technology in specialist WMS.

10.1136/bmjopen-2025-109111.supp2Supplementary data
